### Sample Size

The sample size was calculated using a G*power of 3.1.4. The effect size was calculated as 0.28 based on the BBS from a study reported by Koch et al. (2018). To achieve 95% power with an alpha error of 5%, a sample size of 30 patients will be required. Allowing for a dropout rate of 20%, at least 38 patients are necessary. To ensure enough power to detect this typical difference, we will aim to recruit 40 patients (20 patients per group).

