### Statistical Analysis

#### Clinical Data Analysis

The SPSS (version 22.0, Chicago, IL, United States) statistical software will be used for data analysis. The difference will be considered statistically significant when the *P*-value ≤ 0.05 in two-tailed test. The assumption of normality will be verified by normal probability plots and the Shapiro–Wilk test. Continuous variables with normal distribution will be described as the mean (standard deviation) and analyzed by an independent-samples *t*-test. For abnormally distributed variables, the data will be described as medians with ranges and compared by Mann–Whitney U test (non-parametric tests). Categorical variables will be expressed as frequency (percentage) and Chi-square test or Fisher’s exact test will be used. Repeated measures analysis of variance (ANOVA) will be used to analyze value changes of BBS, FMA-LE, and MBI across four testing time points (weeks 0, 1, 2, and 3). When the interaction is significant, *post hoc* analysis will be conducted, and the Bonferroni adjustment will be used for paired comparisons. Data on clinical scales will be based on per-protocol (PP) and intention-to-treat (ITT) analyses (Sanchez and Xun, 2010). The PP is usually defined as subjects who complete at least 80% of the treatment protocol (Zhao et al., 2021). An ITT analysis include all the patients recruited in the study, irrespective of whether they completed the study period or not. The missing values will be imputed using a multiple imputation method.

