#### Functional Magnetic Resonance Imaging Data Analysis

On the MATLAB R2013b (Mathworks, Natick, MA, United States) platform, the statistical parametric graph software (SPM12.0^1^) and data processing assistant for rs-fMRI software (DPARSF^2^) will be used for data processing and analysis. DPARSF is a SPM-based rs-fMRI data processing software (Yan et al., 2016). Preprocessing steps include (Lv et al., 2018; Ll et al., 2020): (a) removing the first 10–20 time points and slice timing, (b) head movement correction (head movement exceeding 2 mm in any direction or head rotation exceeding 2° will be ruled out), (c) normalization (in accordance with the Montreal Neurological Institute EPI template, each voxel is resampled to 3 mm × 3 mm × 3 mm), (d) delinear drift, (e) removal covariate (confounding effects of head movement parameters, white matter, and cerebrospinal fluid signals), (f) filter (0.01–0.1 Hz), and (g) smooth (8 mm full-width half-maximum Gaussian). Then, the ReHo, fALFF, and FC values will be calculated. The ReHo analysis is a voxel-based measurement that calculates the Kendall coefficient of concordance between a voxel and its surrounding 26 voxels, which is the ReHo value of that voxel (Zang et al., 2004). The ReHo analysis determines the synchrony of adjacent regions, and high values indicate high consistency of regional brain activity. The ALFF measurement is the root mean square of the power spectrum of the BOLD signal in the range of 0.01–0.1 Hz for each voxel. Afterward, the ALFF value of each voxel divided by the full-band ALFF sum is the fALFF value, which can reflect the strength of brain self-activity (Toole et al., 2005). FC was examined by using a seed voxel correlation approach. The cerebellar vermis will be selected as the seed region based on the stimulation target. In SPM12, after bandpass filtering and linear-trend removal, a reference time series for the seed will be extracted by averaging the fMRI time series of voxels. Then, correlations will be computed between the seed reference and the rest of the brain in a voxelwise manner. Finally, an individual relativity value (*r*-value) map will be created, and the correlation coefficients in each voxel will be transformed to *z* values by using Fisher’s *r*-to-*z* transformation to improve normality before performing random effect *t*-tests. The AlphaSim will be used for correction to obtain the adjustment statistical threshold value of *P* < 0.05. Data will be analyzed by the independent-samples (between-group comparison) or paired (within-group comparison) *t*-test.

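### AlphaSim is the only multiple-comparison control for the rs-fMRI maps, and its corrected P < 0.05 is assured only if the map noise has Gaussian spatial correlation of the assumed width

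*Protocol article*

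**What the plan says.** The section Functional Magnetic Resonance Imaging Data Analysis resamples the images ("each voxel is resampled to 3 mm × 3 mm × 3 mm") and smooths them ("smooth (8 mm full-width half-maximum Gaussian"). It then derives three kinds of map: "Then, the ReHo, fALFF, and FC values will be calculated". For FC, with the vermis as seed, "correlations will be computed between the seed reference and the rest of the brain in a voxelwise manner". The tests are described thus: "Data will be analyzed by the independent-samples (between-group comparison) or paired (within-group comparison" *t*-test).

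The control of false positives across voxels is one sentence: "The AlphaSim will be used for correction to obtain the adjustment statistical threshold value of" P < 0.05. No other map-level correction is named. The Bonferroni rule under Clinical Data Analysis ("the Bonferroni adjustment will be used for paired comparisons") concerns BBS, FMA-LE and MBI. Table 1 lists the three rs-fMRI analyses among the key secondary outcomes. Under Sample Size, "we will aim to recruit 40 patients (20 patients per group").

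**The concern.** AlphaSim generates null maps whose spatial correlation is Gaussian with one width, records the largest cluster in each, and uses the 95th percentile as the cut-off. If the real noise keeps some correlation at longer distances than that model allows, large chance clusters are commoner than the simulation predicts. The cut-off is then too small, even when the fitted width agrees with the data at short range.

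The mechanism part of the trial is at stake. Clusters reported as significant at a corrected 0.05 would be read as evidence of remodelling linked to the stimulated vermis, from at most 20 patients per arm. If the true error rate is above 0.05 by an unknown amount, that evidence is weaker than stated.

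**Working it through.** **Taken from the article.** 3 mm isotropic voxels, 8 mm Gaussian smoothing, AlphaSim at corrected P < 0.05, and whole-brain voxelwise maps for FC.

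**Assumed, because the article gives no figure.** An ellipsoid mask of about 62,000 voxels, two-sided voxel thresholds, and the shape of the noise correlation. The last was modelled as a Gaussian part plus an exponential tail:

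ρ(r) = a·exp(−r²/2b²) + (1 − a)·exp(−r/c)

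Here r is distance, 1 − a is the tail weight and c is the decay length. Setting a = 1 gives the AlphaSim model.

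**Step 1: the ideal case.** With Gaussian noise of 8 mm FWHM (61,656 voxels, 500 fields, edge-connected clusters), the 95th percentiles of maximum cluster size were 54 voxels at voxel p<0.01 and 18 at p<0.001. Applied to 500 new Gaussian fields, they gave family-wise error of 6.6% and 7.2%. The Monte Carlo error is √(0.05 × 0.95/500) ≈ 1.0 point for the test fields. It becomes about 1.0 × √2 ≈ 1.4 points once the calibration fields are counted. The results are compatible with 5%, so the procedure does what it claims when its model is right.

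**Step 2: tails added.** For each field type, the FWHM was estimated from its own correlation at one voxel (3 mm). The AlphaSim cut-off was recalculated at that FWHM and applied to null fields with the tail. The figures are per-map family-wise error for a nominal 5%.

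| Tail weight | Decay | Voxel p<0.01 | Voxel p<0.001 |
|---|---|---|---|
| 5% | 9 mm | about 6–8% | about 5–8% |
| 10% | 9 mm | up to about 17% | about 8% |
| 20–40% | 12–16 mm | 26–53% | 14–20% |
| 30–50% | 15–18 mm | 40–57% | 17–32% |

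The first two rows come from runs of 200 and 300 fields, with Monte Carlo error of about 1.5–2 points or more. The third row has b = 5.5 mm and 500 fields. The fourth has 250 fields and face-connected clusters.

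In the third row, the width is not misjudged by much: the estimated FWHM was 8.2–8.7 mm. At 20% weight and 12 mm decay (FWHM 8.6 mm) the cut-offs were 66 and 22 voxels, and the error was 25.8% at p<0.01 and 14.4% at p<0.001. The inflation comes from the tail, which one width cannot represent.

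**Step 3: reading the table.** A stricter voxel threshold reduces the inflation but does not remove it when tails are heavy. With a 5% tail, the result is hard to tell from the nominal level.

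**Limits.** The fields are *z* maps, so small-sample *t* effects are left out. The figures are for one map. They do not address multiplicity across the three metrics or across the between- and within-group tests.

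**The case against.** The strongest objection is that nothing in the article shows long-tailed noise. It has no residual maps, smoothness estimates or autocorrelation data, and in the Gaussian case AlphaSim holds about 5%. That stands. A reader might infer that the claimed P < 0.05 is simply not achieved, or that error rates of 40% and more are to be expected. The documents support neither. Mild tails give only a few points of excess at p<0.001.

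A second tempting reading is that AlphaSim will be run at the nominal 8 mm although the maps are smoother than that. A mismatch of this kind would matter: with true smoothness of 9 mm and a cut-off set at 8 mm, error was 19% at p<0.01 and 10.5% at p<0.001. But the article gives 8 mm as a preprocessing step and never says that AlphaSim will use it in place of an estimated width. This scenario shows sensitivity and is not a finding about the plan.

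Third, the article states no voxel threshold, mask or cluster cut-off. A condensed protocol may leave these to a fuller document, so their absence is not counted here.

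Finally, only secondary outcomes are touched. That is correct and limits the weight of the point. What remains is that the article does fix the method, attaches an error rate to it, and that rate depends on a noise model nothing in the article checks.

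**Conclusion.** The point holds in conditional form. AlphaSim is the sole multiple-comparison control for the three sets of maps, and its corrected P < 0.05 is assured only under Gaussian spatial correlation of the assumed width. Across the tail shapes tried, per-map family-wise error was about 5–8% (mild) to about 14–32% (heavy) at voxel p<0.001, and about 6–17% to about 26–57% at p<0.01. These ranges rest on assumed tails (mild: 5–10% weight, 9 mm decay; heavy: 20–50%, 12–18 mm), an assumed mask, and a width estimated from the field itself. They are not estimates for this trial. The change is worth making because a method that does not need the assumption is available at little cost. The primary BBS analysis and the sample size are not affected.

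**What to change.** Replace AlphaSim with permutation-based family-wise correction at P < 0.05 within a mask set in advance. Either TFCE or maximum cluster size at a fixed voxel p<0.001 would serve, with for example 5,000 permutations.

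- **Between-group test:** compare change maps (post minus pre) and permute arm labels within the two BBS strata (0–20 and 21–40) given under Randomization, so that the permutations match the allocation. The article does not say that the between-group test uses change maps, so this should be written in explicitly.
- **Within-group paired tests:** arm-label permutation does not apply. Flip the signs of the individual difference maps. This assumes that differences are symmetric about zero under the null. Even with 15 patients per arm (half of the required 30) there are 2¹⁵ = 32,768 sign patterns, enough for 5,000 draws.

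The cost is computing time and a change of wording, made before the maps are analysed. No new data are needed. Fewer clusters may survive than under AlphaSim.

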## Materials and Methods

### Study Design

This study will be carried out in the Department of Rehabilitation, Tongren Rehabilitation Hospital, Wuxi, China. Before the conduct of formal experiments, a research coordinator who is responsible for recruitment will arrange a conversation with potential participants to discuss some details, including research purpose, procedures, and the potential risks and benefits. Once informed consent is signed by the patient or their legal guardians (if the patient cannot write independently or consider consent), a questionnaire and baseline assessment will be arranged.

All participants will be randomly assigned to real or sham iTBS and then receive routine rehabilitation treatment, and they will be assessed using the BBS, Fugl–Meyer assessment of the lower extremity (FMA-LE), and modified Barthel index (MBI). Moreover, rs-fMRI scans will be performed at baseline and 3 weeks after treatment. The study flow chart is shown in Figure 1. All baseline data gathering, follow-up assessment, and interventions will be carried out by well-trained researchers with the support of academic staff. This study has been approved by ethics committees (WXMHCIRB2021LLky132) and registered on www.chictr.org.cn on 27 October 2021 under the number ChiCTR2100052590. Details are shown in Table 1.

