Key inclusion and exclusion criteria	Inclusion criteria: (a) have a diagnosis of stroke confirmed by CT and/or MRI, (b) have their first-ever unilateral ischemic stroke between 1 and 6 months of onset, (c) are 40–75 years old, (d) presented with a balance dysfunction with a Berg score between 0 and 40, (e) can follow simple verbal commands or instructions, and (f) can cooperate in signing informed consent forms. Exclusion criteria: (a) with contraindications involving TMS and fMRI (e.g., intracranial implant, cardiac pacemaker, implanted drug pumps, and pregnancy), (b) with cerebellum or brainstem stroke, (c) with balance dysfunction before stroke, (d) with serious diseases that may contribute to condition progression, (e) with severe deficits in communication or executing commands that prevent cooperation with assessment and treatment, (f) who are taking psychotropic drugs, and (g) who are currently enrolled in other clinical trials.
Study type	Interventional Allocation: randomized intervention model Masking: participants and assessors-blinded Assignment: parallel Primary purpose: treatment
Date of first enrolment	Not yet started
Target sample size	40
Recruitment status	Recruiting
Primary outcome(s)	Berg balance scale
Key secondary outcome(s)	Lower extremity of the Fugl–Meyer assessment; modified Barthel index; regional homogeneity, fractional amplitude of low frequency fluctuation and functional connectivity analyses from rs-fMRI.

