### Participants

#### Inclusion Criteria

The inclusion criteria are as follows. Participants who (a) have a diagnosis of stroke confirmed by CT and/or MRI, (b) have their first-ever unilateral ischemic stroke between 1 and 6 months of onset, (c) are 40–75 years old, (d) presented with a balance dysfunction with a Berg score between 0 and 40, (e) can follow simple verbal commands or instructions, and (f) can cooperate in signing informed consent forms.

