## Discussion

This 3-week randomized controlled clinical trial aims to study whether cerebellar vermis iTBS can improve balance function in patients with stroke. In this perspective of experiment design, our study puts forward some methodological concerns that should be discussed, including the large variation in balance function among enrolled patients. Therefore, a stratification approach will be adopted in this study to divide all participants into two subgroups in accordance with the BBS. In addition, we set a sham stimulation group to eliminate the placebo effect of iTBS intervention. After careful consideration of all factors, including the feasibility of the study and the treatment time pattern of the hospital where the experiment will be conducted, we set sessions from Monday to Friday for 3 weeks. Also, outcome will be evaluated at pre-intervention, the end of first, second, and third week of post-intervention. We want to compare the efficacy at different time points, and to explore the earliest time when the treatment can take effect. Our study will use rs-fMRI rather than task state fMRI for measuring the iTBS-induced effects, although task state fMRI can reflect the fMRI images of the brain when performing specific tasks. What we considering is that our subjects are post-stroke patients with motor dysfunction, there may be great differences in the quality of tasks completed by stroke patients, which may affect the results.

In this study, we expect that the cerebellar vermis iTBS can promote the recovery of balance function after stroke. This hypothesis is based on the following evidence.

Maintaining balance depends upon a complex coordination and integration of multiple systems in the body, including the visual system, vestibular system, and auditory system. As pointed out in fMRI research, the cerebellar vermis and the visual network have a strong functional connection (Kellermann et al., 2012; Li et al., 2012). Recent evidence displayed that the vermis coordinates eye and body movements, and provides visual and auditory input related to balance (Fujita et al., 2020). In addition, studies have shown that the vermis participates in regulating vestibular system and maintaining head position (Lam et al., 2016). Balance is best maintained when all inputs are integrated together. Therefore, the cerebellar vermis plays an essential role in the active maintenance of body balance.

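### The fMRI outcomes get a between-arm or a within-arm t-test, with no baseline-adjusted or change contrast named; the within-arm tests cannot attribute change to iTBS

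*Protocol article*

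**What the plan says.** The section Functional Magnetic Resonance Imaging Data Analysis gives the group-level analysis in one sentence: "Data will be analyzed by the independent-samples (between-group comparison) or paired (within-group comparison") t-test. It does not say whether the between-group test takes follow-up maps or change maps, and it does not say which of the two tests decides the mechanistic question. On the threshold it adds: "The AlphaSim will be used for correction to obtain the adjustment statistical threshold value of" P < 0.05.

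Four other places bear on this.

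- Study Design: "rs-fMRI scans will be performed at baseline and 3 weeks after treatment", so each patient has a baseline scan.
- Table 1 lists as key secondary outcomes "regional homogeneity, fractional amplitude of low frequency fluctuation and functional connectivity analyses from rs-fMRI".
- Discussion: "Our study will use rs-fMRI rather than task state fMRI for measuring the iTBS-induced effects". The imaging is therefore meant to support a statement about the stimulation itself.
- Clinical Data Analysis: "Repeated measures analysis of variance (ANOVA) will be used to analyze value changes of BBS, FMA-LE, and MBI across four testing time points", with post hoc tests "When the interaction is significant". This model is written for the three clinical scales only.

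**The concern.** A paired test within the iTBS arm measures everything that happened to those patients over three weeks. Under Intervention, both arms receive 60 minutes of balance-directed rehabilitation after each of 15 sessions. Under Inclusion Criteria, patients "have their first-ever unilateral ischemic stroke between 1 and 6 months of onset" are eligible, a period in which some recovery without stimulation is plausible. A change from baseline in the iTBS arm can therefore arise with no effect of iTBS at all, and a significant result in one arm beside a non-significant result in the other is not a test of the difference between them.

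The between-arm test does use the randomisation. Without any mention of the baseline scan, though, its plainest reading is a comparison of follow-up maps alone, in arms of about 15 to 20, with information already collected left unused.

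What is at stake is the mechanistic conclusion. With two tests listed side by side and neither marked as deciding, that conclusion could rest on the paired results.

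**Working it through.** **The plan's own figure.** The article gives no sample size or power for the imaging. Its only figure is for the Berg scale (Sample Size): effect size 0.28, alpha 0.05, power 95%, N = 30, raised to 38 for 20% dropout. Reading 0.28 as Cohen's f in a repeated-measures ANOVA with 2 groups and 4 measurements, and assuming correlation 0.5 and sphericity (neither is stated), λ = f²·N·m/(1 − ρ) = 0.28² × 30 × 4 / 0.5 = 18.8 on 3 and 84 degrees of freedom. Power is 0.959, and 30 is the smallest even N that reaches 0.95. Then 30/0.8 = 37.5, rounded up to 38. The figure reproduces. It fits an arm-by-time interaction, but a time main effect gives the same 30 under these settings, so it does not show which contrast was intended. It supplies only the evaluable number used below, 15 per arm.

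**Step 1: paired tests read arm by arm.** Suppose both arms change equally and each paired test has power p. The arms contain different patients, so the two results are independent.

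- Exactly one arm significant: 2p(1 − p). At p = 0.5 this is 0.50; at p = 0.8 it is 0.32.
- iTBS arm alone significant: p(1 − p). At p = 0.5 this is 0.25; at p = 0.8 it is 0.16.

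The same check with exact paired-t power at 15 per arm, for an assumed equal standardised change dz in both arms:

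| dz | power of each test | exactly one arm | iTBS alone |
|---|---|---|---|
| 0.3 | 0.192 | 0.310 | 0.155 |
| 0.5 | 0.438 | 0.492 | 0.246 |
| 0.8 | 0.821 | 0.294 | 0.147 |

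**Step 2: validity of the between-arm test.** Two randomised arms of 15 with no arm effect were simulated at pre–post correlations r = 0.3, 0.5 and 0.7 (40,000 trials each). The t-test on follow-up values alone rejected in 4.9% to 5.1% of trials, and so did the t-test on change. Both hold the 5% level.

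**Step 3: precision.** Relative to a follow-up-only test, residual variance is multiplied by 1 − r² with baseline as covariate and by 2(1 − r) with a plain change score. The power columns take an assumed effect of 0.8 SD, 15 per arm and two-sided 0.05; the covariate column is approximate.

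| r (assumed) | 1 − r² | 2(1 − r) | power, follow-up only | power, change | power, covariate |
|---|---|---|---|---|---|
| 0.3 | 0.91 | 1.40 | 0.56 | 0.43 | 0.60 |
| 0.5 | 0.75 | 1.00 | 0.56 | 0.56 | 0.69 |
| 0.7 | 0.51 | 0.60 | 0.56 | 0.78 | 0.84 |

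Over r = 0.5 to 0.7 the covariate removes 1 − 0.75 = 25% to 1 − 0.51 = 49% of the residual variance. The change score gains nothing at r = 0.5 and loses at r = 0.3. The covariate form is the best of the three in every row.

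These figures are for a single region or voxel at unadjusted 0.05. Power under the AlphaSim-corrected voxelwise threshold would be lower.

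**The case against.** The strongest defence is that the article does plan a between-group test on randomised arms and simply does not name its input. Run on pre–post difference maps, an independent-samples t-test is a test of the arm difference in change. A condensed article may leave that detail to a fuller document, and the paired tests may be meant only as description beside it.

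Much of this stands. A reader might infer that the plan never tests the arm difference in change; the text does not establish that, because it is silent on which maps enter the test. A reader might also infer that the plan cannot attribute any brain change to iTBS. That fails even on the least favourable reading: a comparison of follow-up maps between randomised arms holds its 5% error (Step 2), and chance baseline differences are already covered by that error rate. The loss there is precision. Nor does the article say that the investigators would read discordant paired results as a difference between arms.

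Two things remain. This section is specific about voxel size, filter band, smoothing kernel, seed, cluster correction and the tests themselves, so the choice of tests is stated here and not merely left open. And it sets the paired tests beside the between-group test without saying which one supports the inference, while the clinical section shows that the interaction structure was available.

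**Conclusion.** The point holds in a limited form. For three key secondary imaging outcomes the article names no baseline-adjusted or change contrast, and it lists a within-arm test that cannot separate iTBS from rehabilitation and recovery.

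If the paired tests were used for inference, with equal true change in both arms, the iTBS arm alone would be significant 25% of the time at 50% power and 16% at 80% power. It is tempting to quote 50% and 32% as the rate of a false iTBS-only finding, but those figures count either arm. If the between-arm test uses follow-up maps only, the result is valid but gives up a 25% to 49% reduction in residual variance at r = 0.5 to 0.7. The document gives no pre–post correlation or imaging effect size, so both are assumptions.

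A reader might further infer that left- and right-sided lesions are pooled without alignment. The article is silent on this, and mirroring images is a debatable preprocessing choice, so no finding is made on it.

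This should be corrected, at very little cost. It touches the mechanistic outcomes and leaves the primary analysis of the Berg Balance Scale as it is.

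**What to change.** Replace the sentence on group-level tests with one inferential test for each of ReHo, fALFF and functional connectivity: a between-arm comparison of the 3-week maps, with the patient's own baseline map as covariate (voxel by voxel, or as regional values where that is easier) and the Berg randomisation stratum (0–20 or 21–40) as a further term. Prefer this to a plain difference of maps, which gains nothing at r = 0.5 and loses precision below it. State that within-arm paired maps are descriptive and that no claim about iTBS rests on them. Settle this before unblinding, so that the choice between tests cannot follow the results.

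The cost is a sentence, one extra design matrix and two degrees of freedom: with 30 patients, 30 − 2 = 28 becomes 30 − 4 = 26. No further patients, scans or visits are needed.
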